### Statistical Analyses

Quantitative data will initially be screened for assumptions, including univariate and multivariate normality, and tested for the presence of outliers. Further, quantitative analyses will be complemented with effect sizes (which will be reported and interpreted according to guidelines) [59].

As for phase 1, we will test the longitudinal changes over time in PSMU as well as its psychosocial predictors, or the interactions between psychological distress (anxiety and depression) and PSMU, through 3-level mixed models (with repeated measures nested within participants, nested within classes) [60]. Ecological momentary assessment data will be examined through multilevel regression models, to test the interaction effects between SM use and emotional experiences over time. Finally, longitudinal profiles of participants will be examined through latent growth curve analyses [61]. Due to the relevant changes within adolescence, sensitivity analyses (based on sociodemographic variables, including age groups such as 14-15 years and 16-18 years) will also be carried out.

As for phase 2, each FG will be audio-recorded and transcribed verbatim. The transcribed text will be thematically analyzed using a 6-phase process for data engagement, coding, and themes development [62-64]: (1) familiarization with data and starting to create initial observations; (2) generation of initial codes; (3) searching for themes and discussion on how to combine and cluster different codes to form an overarching theme; (4) reviewing the themes checking them against the original data; (5) defining and naming themes; and (6) for each theme, representative quotes to contextualize and exemplify the themes will be selected to tell the reader a coherent story about the data. Analyses will be conducted by considering the recurrence but also meaningfulness as main criteria during the coding process. An inductive approach will be predominant [65,66]. However, to ensure that results will be meaningful to the research questions, in addition codes might be developed keeping in mind the main theoretical models of PSMU (such as the Multidimensional Model of Social Media Use [13], the Interaction of Person-Affect-Cognition-Execution model [67], and the pathway model [68]). To enhance rigor and trustworthiness of these procedures and analyses [69], and in accordance with Lincoln and Guba [70] credibility, transferability, dependability, and confirmability criteria, multiple strategies will be introduced. These will include prolonged engagement; persistent observation; 2 independent researchers will analyze the data separately; investigator triangulation by involving several researchers as research team members and presenting analysis at data group meetings; detailed descriptions of the research context to facilitate the assessment of its relevance and applicability to other contexts; purposeful sampling to ensure a diverse range of participants; reflexivity and researcher positionality; and maintaining an audit trail; and using transparent approaches to data analysis [69].

Finally, examples and scenarios will be stimulated during the discussion and might be used to inform the app (eg, collecting real-life examples of PSMU; situations in which negative experiences with SM are associated with well-being; protective strategies to PSMU).

In line with a mixed methods approach [71], quantitative and qualitative results will be synthesized and merged in order to achieve a better understating of the PSMU. Indeed, qualitative results will be used to deepen our understanding of the PSMU phenomenon, corroborating the findings from the quantitative design and/or adding potential different topics.

As for phase 3, feasibility (ie, uMARS mean scores and app usage) will be investigated through simple descriptives, examining whether participants met the thresholds for good feasibility: (1) mean uMARS subscale scores≥70% of the total will be considered indicative of good feasibility [72]; examining the app use (with ≥75% of participants with ≥10 app sessions considered indicative of a good feasibility) [72]. We will have a deeper understanding of the app feasibility by synthesizing the qualitative results. We will further examine whether the self-help app led to an actual change in primary and secondary outcomes through 3-level piecewise regression models, using the 4-time points from baseline (as defined in phase 1; T0) up to posttreatment (T3; M18-M20). To further strengthen these analyses, we will compute both a Reliable Change Index and a Clinically Significant Change for each participant [73,74]. These methods are used to test whether a change over time (in our case, from pre- to posttreatment) may be considered reliable (ie, taking into account the measure’s internal reliability) and clinically significant (eg, the posttreatment scores are within the boundaries of nonpathological scores).

Quantitative analyses will be performed using SPSS (version 29; IBM Corp), Hierarchical Linear Models (version 8.2; Scientific Software International, Inc), and MPLUS (version 8.4; Muthén & Muthén).

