## Methods

### Study Design

The SMART project is organized in 3 consequential phases, each including different integrated actions: phase 1—prospective longitudinal study with repeated-measures design [32] for the advancement of knowledge on PSMU through quantitative approaches; phase 2—qualitative focus group study for exploring adolescents’ perspectives on PSMU and functional use of SM and co-design approach for developing the unguided self-help SMART app; phase 3—pilot study to evaluate feasibility and signal of effectiveness of the intervention throughout the self-help app.

The project is conducted by researchers and clinical psychologists in four Italian Universities (University of Verona, University of Palermo, University of Perugia, and University of Bergamo), thus including a large population of midadolescents in diverse regions of north, central, and south of Italy (see Figure 1 for an overview of the project phases and Table 1 for a synthetic description of general objectives, research aims, and methods of each phase).

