### Participant Recruitment and Setting

The target group (adolescents aged 14-18 years) will be actively involved in the various actions of each phase. Participants will be recruited from schools (ie, secondary school), in the north, central, and south Italy. Each research team will select schools (on a voluntary basis or following previous collaborations) and interact with stakeholders (regional and local school offices, school communities) to obtain their availability for participation. Attention will be given to contacting schools located in particularly disadvantaged areas and to include students with different sociodemographic and cultural backgrounds and levels of vulnerability. At each participating school, adolescents may participate in the different phases of the study.

The following inclusion criteria will be followed for participation in each included school: (1) having an age between 14 and 18 years, (2) having signed the consent form for the study participation (ie, consent to participate for adolescents less than 18 years signed by both parents—or legal representatives—or by the adolescent when 18 years); having sufficient knowledge of the Italian language.

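### The models stop at class level although pupils are recruited through schools, so tests of mean change can be too liberal if change differs between schools

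*Protocol article*

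**What the plan says.** **Sampling.** Under Participant Recruitment and Setting: "Participants will be recruited from schools (ie, secondary school), in the north, central, and south Italy". Schools are picked locally: "Each research team will select schools (on a voluntary basis or following previous collaborations". They are meant to be varied: "Attention will be given to contacting schools located in particularly disadvantaged areas". The same schools feed all phases: "At each participating school, adolescents may participate in the different phases of the study". Study Design adds the centres: "The project is conducted by researchers and clinical psychologists in four Italian Universities".

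**Analysis.** Under Statistical Analyses, phase 1 change in problematic social media use (PSMU) and its predictors are tested "through 3-level mixed models (with repeated measures nested within participants, nested within classes". For phase 3, the article examines "change in primary and secondary outcomes through 3-level piecewise regression models, using the 4-time points from baseline" to post-treatment. It does not name the three levels there. Class as the top level is an inference from phase 1.

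**What is not mentioned.** The article mentions no random level, fixed factor or clustered standard error for school or site. Sample Size Estimation does not mention clustering. The planned sensitivity analyses use sociodemographic variables, with age groups as the only named example.

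**The concern.** The school is the unit through which pupils enter the study, and one school may contribute several classes. Three named levels are used up by wave, participant and class. Two classes from one school are then treated as being as independent as two classes from different regions.

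The article itself gives grounds for expecting some school-specific change. Surveys are completed in school hours. Each wave spans a three-month window (months 3–5, 8–10, 13–15), so dates and intervals may differ by school. Schools also differ in region and disadvantage.

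At stake are two tests that average change over schools: mean change in PSMU over the waves (phase 1), and the T2–T3 piece used to judge whether the app led to a change (phase 3, single arm). If schools differ in change, the precision of these averages depends on the number of schools as well as on the number of classes. A model that ignores this reports standard errors that are too small.

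**Working it through.** **Plan's own figure.** 1216 × 1.25 = 1520, as stated. It carries no information on clustering and is used here only to size the layouts.

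**Inputs from the article.** About 1216 pupils analysed in phase 1 and about 400 expected in phase 3. The three levels are as quoted.

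**Assumed inputs (not in the article).** S schools, K classes per school, n pupils per class. The change score has total variance 1, with school share s, class share c = 0.02 and pupil share e = 1 − s − c. Layouts of 20 × 3 × 20 (1200 pupils), 12 × 5 × 20 (1200) and 8 × 8 × 19 (1216) stand for phase 1. Layouts of 20 × 3 × 7 and 12 × 5 × 7 (420 each) stand for phase 3. The class-level model is given a random class slope, which favours the plan.

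**Step 1: level or change?** If schools differ only in average level, the weights of a within-pupil time contrast sum to 0 and the school effect drops out. A generalised least squares check (6 schools × 4 classes × 12 pupils, 25% dropout, school and class variance 0.03 each) gives a true/model variance ratio of 1.00 for time and 1.77 for the overall mean level. So only school variance in *change* matters for the time tests.

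**Step 2: formula for mean change.** Let u = c + e/n.

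- The true variance of the mean change is (K·s + u)/(S·K).
- The class-level model estimates, on average, [s·(1 − (K−1)/(SK−1)) + u]/(S·K).
- The ratio is R = (K·s + u)/[s·(1 − (K−1)/(SK−1)) + u].
- Type I error ≈ P(|Z| > t/√R), with t the critical value on SK − 1 degrees of freedom.

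**Step 3: worked case, phase 1, 12 × 5 × 20, s = 0.02.**

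- e/n = 0.96/20 = 0.048, so u = 0.068.
- Numerator: 5 × 0.02 + 0.068 = 0.168.
- Denominator: 0.02 × (1 − 4/59) + 0.068 = 0.0866.
- R = 1.94 and √R = 1.39; 2.001/1.39 = 1.44, so the error is about 15%. Simulation gives 15.7%.

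**Step 4: same layout in phase 3, n = 7.** u = 0.02 + 0.96/7 = 0.157 and R = 0.257/0.176 = 1.46. Simulation gives 10.5%. Fewer pupils per class mean more pupil-level noise, so the omitted school part weighs less.

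**Step 5: grid.** Type I error at nominal 5%, 20,000 simulated data sets per cell, class as top level:

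| Layout | s = 0 | 0.01 | 0.02 | 0.05 |
|---|---|---|---|---|
| Phase 1, 20 × 3 × 20 | 5.0% | 8.0% | 10.3% | 14.9% |
| Phase 1, 12 × 5 × 20 | 5.0% | 11.1% | 15.7% | 24.1% |
| Phase 1, 8 × 8 × 19 | 5.0% | 15.0% | 21.7% | 33.1% |
| Phase 3, 20 × 3 × 7 | 4.8% | 6.2% | 7.4% | 10.9% |
| Phase 3, 12 × 5 × 7 | 4.8% | 7.9% | 10.5% | 16.9% |

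With school as the top unit, every cell lies between 4.6% and 5.3%. With one class per school (K = 1), R = 1 and the class-level test is correct at about 5%.

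**Step 6: pupil-level predictors.** In simulation with a class random intercept and no school term, the test of a pupil-level predictor has a type I error of 5.1–6.1%.

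**The case against.** **The tests need not be too liberal at all.** A reader might infer that omitting the school level makes the time tests invalid outright. The article does not support that. The inflation needs school variance in change, for which it gives no figure, and more than one class per school, which it does not state. Shared intake or phone rules mainly shift level, and level cancels. This part of the objection stands, and the point is conditional.

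**The stated hypotheses are mostly untouched.** Aim 1 concerns intrapersonal and interpersonal predictors, and aim 3 relates amount of app use to functional use. Both work through pupil-level variables, which are hardly affected. A reader might conclude that the risk-factor findings are compromised; they are not. Mean change is nonetheless tested in both phases.

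**Region contrasts.** It is tempting to add that comparisons of areas would be wrong. The article names no such comparison, so none is counted here.

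**Phase 3.** The class level is inferred, the app is unguided and freely downloaded, and the phase is a single-arm pilot whose numerical thresholds are descriptive. The article already concedes that the nonrandomised design limits causal inference. The phase 3 concern is therefore the weaker half.

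**An article is brief.** Naming the random levels does not exclude school as a fixed effect or clustered standard errors in a fuller plan. That is fair. However, the article does more than leave the nesting open: it states one, and that nesting does not match its own sampling.

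**Conclusion.** The mismatch is real: recruitment is by school, the stated phase 1 hierarchy ends at class, and phase 3 appears to follow it. The consequence is conditional. If change in PSMU differs between schools and schools contribute several classes, the tests of mean change can be too liberal.

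On the assumed layouts, phase 1 type I error runs from about 5% to roughly 10–20% at school shares of 0.02–0.05. It goes above that only in the harsher cells (24% with 12 schools, up to 33% with 8). Phase 3 is milder, at about 7–17% over the same shares. No single figure should be quoted as the plan's error rate, because the number of schools, classes per school and variance shares are all assumed.

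This is a cheap improvement to the wording of the analysis, not a defect that undermines the main risk-factor analyses.

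**What to change.** In Statistical Analyses, for both phase 1 and phase 3, state how school is handled in the tests of mean change:

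- **Preferred:** add school as a fourth level with a random time slope (in phase 3, for the T2–T3 piece). A school random intercept alone would not help, because level differences already cancel.
- **If schools are few or the model does not converge:** keep the 3-level model and use standard errors clustered on school with a small-sample correction.
- **If site is entered as a fixed factor:** include site-by-time. A site main effect does nothing for the mean-change test.
- Name the three levels in the phase 3 model, and report the number of schools and of classes per school.

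**Cost.** A few lines of text and slightly more modelling. School membership should be known from recruitment. Intervals for mean change become somewhat wider and have fewer degrees of freedom. If schools turn out not to differ in change, the price of testing at school level is about the ratio of critical values: 2.093/2.001 = 1.05 with 20 schools of 3 classes, 2.201/2.001 = 1.10 with 12 of 5, and 2.365/1.998 = 1.18 with 8 of 8.

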**Methods:**

The SMART project is organized in 3 phases: phase 1 will focus on knowledge advancement on PSMU and its risk and protective factors using a longitudinal design; phase 2 will explore adolescents perspectives using qualitative approach and will co-design an unguided self-help app for reducing PSMU, which will be evaluated and adapted in phase 3. Around 1500 midadolescents (aged 14-18 years) will be recruited in northern, central, and southern Italy to investigate the potential intra- and interpersonal psychological risk and protective factors for PSMU and define specific PSMU profiles and test for its association with psychological distress. Subjective (self-report) PSMU’s psychosocial risk or protective factors will be assessed at 3 different time points and Ecological Momentary Assessment (EMA) will be used. Moreover, focus groups will be performed in a subsample of midadolescents to collect the adolescents’ unique point of view on PSMU and experiences with SM. Those previous results will inform the self-help app, which will be co-designed through working groups with adolescents. Subsequently, the SMART app will be deployed and adapted, after testing its feasibility and potential effectiveness in a pilot study.

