**Figure 1 figure1:**
[figure not shown]
SMART project: General overview of the 3 phases.

**Table 1 table1:** General description of the 4 study phases: objectives, research aims, and main methodologies.

Phase	General objectives	Research aims	Main methodologies
Phase 1: Longitudinal prospective study	Improving the conceptualization of PSMU^a^ Longitudinally identifying the intra- and interpersonal risk, protective and maintenance factors of PSMU Longitudinally analyzing the associations between PSMU and psychological distress Exploring the presence of specific profiles of PSMU among adolescents Informing the development of SMART self-help app	Which are the main risk or protective factors of PSMU among adolescents? What are the longitudinal associations between PSMU and psychological distress? Is PSMU predicted by a higher distress, or is it a change in distress for that specific participant to predict it? Are there specific sub-groups of PSMU? If yes, what characterizes them?	Prospective longitudinal study with repeated-measures design (3 waves) using self-report questionnaires Collection of biological markers EMA^b^
Phase 2: Qualitative study and co-design of the SMART app	Exploring adolescents’ experiences, examples and perspectives on PSMU and functional use of SM^c^ Informing the development of SMART self-help app Co-designing the beta version of a self-help app aiming to promote awareness and functional SM use	Which are the adolescents’ experiences and perspectives on PSMU and functional use of SM? Which are the adolescents' opinions and perspectives on what is useful to promote awareness and functional SM use? Which are the adolescents’ perspectives, suggestions, and preferences on an app to promote functional SM use?	Focus groups Thematic analysis of the transcripts to identify and analyze patterns in qualitative data Co-design working groups with the adolescents involved
Phase 3: Feasibility and pilot study	Investigating the feasibility and acceptability of the SMART self-help app Preliminary evaluating its effectiveness Incorporating user feedback and study results during the app development	Which are the perspectives of adolescents on the SMART self-help app feasibility and acceptability? Is there preliminary evidence that the SMART self-help app is effective?	Single-arm pilot feasibility study to explore feasibility and preliminary data on effectiveness (pre-post evaluation)

^a^PSMU: problematic social media use.

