## Discussion

### Expected Findings

The innovative SMART project replies to crucial existing knowledge gaps on PSMU. First, to date, the conceptualization of PSMU is still debated. The SMART project emphasizes a person-centered approach since it underlines the need to focus not only on “how much” the SM is used, but also on “how” adolescents engage in this behavior. Second, a comprehensive evaluation of risk or protective factors for PSMU is still lacking. Thus, the potential effect of diverse variables at intra- and interpersonal psychological and biological levels, collected at several time points, is examined. Adopting complex longitudinal data analyses represents a third innovative aspect—as literature in the field relied mostly on cross-sectional designs—allowing us to test several hypotheses whose final aim is to disentangle the longitudinal associations between supposed risk or protective-factors, psychological distress, and the changes over time in PSMU. For example, the definition of different longitudinal profiles of primary or secondary PSMU outcomes will orient the scientific community about new research lines of inquiry and the development of tailored interventions. The adoption of EMA—a promising naturalistic and ecologic research method that provides longitudinally valid data and investigates SM use in real time—will additionally provide a fine-grained picture of adolescents’ experiences in their natural contexts, capturing both the variability over time in SM use, emotional experiences, and their interactive dynamic patterns. Third, an additional strength lies in the use of a mixed-methods design, combining quantitative and qualitative approaches to enrich the understanding of PSMU and of the relationships between the investigated variables.

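### The only phase 1 method named for PSMU profiles, latent growth curve analysis, cannot as written show whether sub-groups exist or what characterizes them

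*Protocol article*

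**What the plan says.** The sub-group aim appears in three places in the protocol article.

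- Abstract, Methods: the study will "define specific PSMU profiles and test for its association with psychological distress".
- Table 1, phase 1: an objective is "Exploring the presence of specific profiles of PSMU among adolescents", and a research question reads "Are there specific sub-groups of PSMU? If yes, what characterizes them".
- Discussion, Expected Findings: "the definition of different longitudinal profiles of primary or secondary PSMU outcomes will orient the scientific community".

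Statistical Analyses gives one method for profiles: "longitudinal profiles of participants will be examined through latent growth curve analyses". The other phase 1 analyses are models of change and predictors "through 3-level mixed models (with repeated measures nested within participants, nested within classes", multilevel regressions of the momentary assessment data, and "sensitivity analyses (based on sociodemographic variables, including age groups such as 14-15 years and 16-18 years". The phase 1 design is a "Prospective longitudinal study with repeated-measures design (3 waves) using self-report questionnaires". Mplus 8.4 is among the listed software.

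**The concern.** The research question is about discrete groups: whether they exist, and what distinguishes their members. A conventional latent growth curve estimates a mean intercept, a mean slope, and their variances and covariance. It treats adolescents as one population that varies continuously, so the number of groups is not a quantity it estimates and nobody is assigned to a group.

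With three waves and linear growth it is also, at participant level, essentially the random-intercept, random-slope mixed model that the same section already plans. It therefore adds little on sub-groups.

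At stake is one stated phase 1 objective and an output that the Discussion presents as a contribution. The analysis as named would return an average slope and its spread. A well-fitting model could be taken as evidence against distinct profiles when it carries no such evidence.

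**Working it through.** The plan gives no figure on this point, so there is none to reproduce. The check has two parts: what each named analysis can return, and what a single growth curve does when sub-groups are really there.

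**1. Named phase 1 analyses set against the sub-group question**

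| Analysis in Statistical Analyses | Groups it can return |
|---|---|
| Latent growth curve | None: one mean trajectory, continuous variation |
| 3-level mixed models | None: one population, random effects |
| Multilevel regression of momentary data | None: one population, random effects |
| Age-band sensitivity analyses | Observed groups fixed in advance, not latent ones |

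No latent class, mixture, latent profile or cluster analysis is named anywhere in the article. The phase 2 focus groups do not identify statistical sub-groups either.

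**2. A single growth curve fitted to two true classes**

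From the article: three waves, and 1216 adolescents (Sample Size Estimation). Assumed for illustration:

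- class shares of 80% and 20%;
- intercept and slope means of 14 and -0.5 in the first class, 18 and +2.5 in the second;
- within-class intercept variance 4 and slope variance 0.3, uncorrelated;
- residual variance 4 at each wave.

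Pooling two classes with shares p and 1-p adds p(1-p) times the squared difference in class means to each variance, and p(1-p) times the product of the differences to the covariance. Here p(1-p) = 0.8 × 0.2 = 0.16. The class means differ by 4 in intercept and 3 in slope.

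- Mean intercept: 0.8 × 14 + 0.2 × 18 = 14.8
- Mean slope: 0.8 × (-0.5) + 0.2 × 2.5 = 0.1
- Intercept variance: 4 + 0.16 × 16 = 6.56
- Slope variance: 0.3 + 0.16 × 9 = 1.74
- Covariance: 0.16 × 4 × 3 = 1.92

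A single growth curve with these five values and residual variance 4 implies:

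- wave means 14.8, 14.9 and 15.0;
- wave variances 6.56 + 4 = 10.56; 6.56 + 2 × 1.92 + 1.74 + 4 = 16.14; and 6.56 + 4 × 1.92 + 4 × 1.74 + 4 = 25.20;
- covariances 6.56 + 1.92 = 8.48 (waves 1, 2); 6.56 + 2 × 1.92 = 10.40 (waves 1, 3); and 6.56 + 3 × 1.92 + 2 × 1.74 = 15.80 (waves 2, 3).

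These are exactly the means and covariances of the two-class mixture. The model uses only means and covariances, so it cannot tell the two situations apart. The class values are assumed, but the identity does not depend on them: it holds for any two linear classes with common within-class variances.

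**3. Does the fit test give a warning?**

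With three waves there are 3 means + 6 variances and covariances = 9 moments. The linear model has 2 means + 3 growth variances and covariance + 3 residual variances = 8 parameters, which leaves 1 degree of freedom. In 200 simulated data sets of 1216 adolescents from the two classes above, the chi-square test on 1 degree of freedom rejected at the 5% level in 4%. The simulation error around 5% is sqrt(0.05 × 0.95 / 200) = 1.5 percentage points, so this is the nominal rate. The model fits well while one group improves and another worsens.

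**The case against.** The strongest reply is that the label may be loose. Growth modelling is a family, the sentence speaks of profiles in the plural, and Mplus fits class-based versions. The reference cited for the sentence would help to settle the meaning, but it is not at hand. This stands as a limit: if a class-based model was meant, the wording is at fault rather than the plan. It does not remove the point, because the sentence would still name a model that does not do the job.

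A second reply is that a condensed article may leave methods to a fuller plan. That covers silence. Here a method is named and attached to profiles, and it does not fit the question.

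Four stronger readings are tempting, and the article does not support them.

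- *The sub-group question will go unanswered.* The study is preregistered, and neither that record nor a full plan is shown. The article shows only that no analysis it names can answer the question. Table 1 also does not restrict sub-groups to trajectories.
- *Any profiles will come from an analysis chosen after seeing the data.* The Results section reports T0 and T1 complete by July 2024, so the risk exists if the model is still open. The article does not show that it is.
- *The app depends on the profiles.* The Discussion mentions adapting the app to different profiles only as possible future research. Adaptation within phase 3 rests on emerging results in general.
- *The main phase 1 conclusions are affected.* The hypotheses under Objectives concern predictors of PSMU, emotional distress and passive use. Those go to the mixed models.

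**Conclusion.** The point holds in a limited form. As written, the one method named for profiles cannot show whether sub-groups of PSMU exist or what characterizes them, and no other phase 1 analysis in the article can. This follows from the structure of the model. The simulation only illustrates it, under assumed class values.

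The severity is moderate. One exploratory phase 1 objective lacks a suitable named analysis. The primary and secondary outcome models, the sample size and the feasibility thresholds are unaffected. The conclusion assumes the usual meaning of latent growth curve analysis. If the authors meant a class-based growth model, only a correction of wording is needed.

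**What to change.** Replace or extend the sentence in Statistical Analyses so that it does the following.

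- Names latent class growth analysis or growth mixture modelling over T0 to T2 in Mplus, for the primary outcome and for any secondary outcome whose profiles will be reported.
- Keeps the single-class growth curve as the 1-class reference.
- States in advance how the number of classes is chosen, for example by BIC with a minimum class size. The rule must be compatible with nesting in school classes. A standard parametric bootstrap likelihood-ratio test simulates independent participants, so it would ignore that nesting.
- Relates predictors to class membership by a bias-corrected step, which answers what characterizes the groups.
- Labels the whole analysis exploratory.

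If the authors already meant such a model, the sentence should say so. If they do not intend one, the sub-group question should come out of Table 1, and the profile statements in the Abstract and Discussion should be reworded to match.

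The cost is a few sentences and some analyst time, with no new data or software. There is one small downside: skewed scores can make mixture models extract too many classes, which is why the rule on class number and size matters.
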